### Data collection

Data collected at 30 days after surgery will be through an online survey, online interviews for a subset of participants, questionnaire-based phone calls and a review of the Isla platform data. 30 days has been chosen as the data collection point as this is the recommended follow-up time for a wound infection as stipulated by the national wound surveillance programme run by the UKHSA.^20^ Further data are collected at 60 days to estimate quality of life and identify events such as hospital readmissions or further surgery which will be used in the health economic analysis. Data collected at 60 days after surgery will be through questionnaire-based phone calls and medical case note review.

Online surveys will be hosted on Dacima. The patient survey will focus on satisfaction with wound follow-up (and acceptability of the platform for intervention group participants only). Staff surveys will focus on satisfaction with wound monitoring including the Isla platform with AI. The survey is expected to take 10 min to complete. Interviews will be conducted via Teams, recorded using digital audio recording and transcribed. The focus of the patients’ interviews will be acceptability of the Isla platform, satisfaction with postoperative wound follow-up and acceptability of taking part in the study. Interviews are expected to last around 40 min. The Isla platform review will be conducted to collect data on the number of images submitted, dates of submissions and discrepancies between Isla wound prioritisation and clinician prioritisation. Phone calls at 30 days will include the UKHSA postdischarge SSI questionnaire to diagnose wound infection status, questions focusing on engagement with National Health Service (NHS) services (including treatment, antibiotics, readmissions, further surgery, GP or hospital visits) and a quality-of-life tool (SF-6Dv2). The phone call at 60 days will focus on engagement with NHS services and will include the SF-6Dv2 quality-of-life tool. Medical case note review will capture demographic data plus readmissions or further surgery.

### Data analysis

Descriptive statistics will be presented to summarise the distribution of baseline variables across each of the randomisation groups. Continuous variables (age, height, weight, body mass index, quality of life) will be reported with means and 95% CI, if shown to be normally distributed, using a combined skewness and kurtosis test, otherwise will be reported with medians and IQR. The categorical and ordinal variables (eg, sex, ethnicity, disability, diabetes, smoker status, skin tone, socioeconomic status, surgical procedure, length of stay, carer status, partner status, owned smartphone, resources given to patient such as ipad, mobile, pay as you go and internet) will be reported with frequencies and percentages.

Safety outcomes, such as the quality of images received and assessed by clinicians at 30 days, will be reported using frequencies and percentages. Qualitative data from the interviews will be analysed using thematic analysis.

For acceptability outcomes, variables that are continuous will be reported with means and CIs, if shown to be normally distributed, using a normality plot, otherwise, they will be reported with medians and IQRs. Categorical variables (eg, sex, ethnicity) will be reported with frequencies and percentages.

Feasibility outcomes relating to adherence will be reported as the number and percentage of adherent patients in the intervention group. To be adherent a patient needs to submit one photo with a completed questionnaire within the 30-day period. This will be compared with the progression criteria defined below (table 1). The definitive study will proceed (or not) based on these outcomes. The number and percentage of eligible patients recruited for the study will be reported. The feasibility outcomes will be reported with 95% CI.

**Table 1 T1:** Progression criteria

Criteria	Do not proceed	Proceed with changes	Proceed
Recruitment	<10% of eligible patients consent	Between 10% and <25% of eligible patients consent	At least 25% of eligible patients consent
Adherence with the module	<40% of intervention patients submit one or more images	Between 40% and <80% of intervention patients submit one or more images	At least 80% of intervention patients submit one or more images
Loss to follow-up	<10% of intervention patients complete the study	Between 10% and <60% of intervention patients complete the study	At least 60% of intervention patients complete the study

For all secondary outcomes, continuous variables will be reported using descriptive methods such as means and 95% CI. Categorical variables will be reported with frequencies and percentages.

There will be no subgroup analysis, no adjusted analysis and no interim analysis.

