#### Sample size

This is a feasibility study, and therefore, sample size calculations cannot be calculated as there are no current data which can be used as the basis of the calculations. The feasibility outcomes for this study are all binary outcomes, for which the widest CIs will occur with a proportion of 0.5 (or 50%), therefore, calculating a sample size for the CI based on 50% gives a ‘worst case’ estimate.

Recruiting 60 patients for each treatment group into the trial (ie, a total of 120 patients) will enable us to estimate the recruitment and drop-out rates with a 95% CI of within ±10% even if the rates were 50% for these two feasibility outcomes. (The 95% CI for a sample size of 120 patients and 60 successes, ie, 50% of patients recruited, or 50% of patients completing the study, is 41% to 59%). If the adherence to treatment rate is 50%, the adherence rate and 95% CI could be estimated to within ±13%. (The 95% CI for 30 adherent patients out of 60, as this is only relevant for patients in the intervention group, is 37%–63%). The sample size estimations were calculated using STATA V.18 with command ‘cii proportions’.

In addition, national data show a wound problem rate of 21% (our data shows 15%) with a cardiac wound infection rate of 8%.^19 20^ A sample size of 120 patients should provide around nine patients in each group with a wound problem of which 4–5 patients should have a wound infection. This is sufficient to inform feasibility, safety and acceptability data.

With a potential sample size of 1300 patients, we plan to recruit 120 patients over 10 months, a recruitment rate of around 11%. This should be achievable as a randomised trial using patients’ smartphones to monitor surgical wounds had a 69% recruitment rate.^9^

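### The loss-to-follow-up progression criterion leaves out the control arm, although drop-out was planned on all 120 patients, and its stop limit needs more than 90% loss

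*Protocol article*

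**What the plan says.** Table 1 (Data analysis section) sets three bands for loss to follow-up, all expressed as completion in the intervention arm:

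- *Do not proceed*: "<10% of intervention patients complete the study"
- *Proceed with changes*: "Between 10% and <60% of intervention patients complete the study"
- *Proceed*: "At least 60% of intervention patients complete the study"

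The text above the table makes the decision on the definitive study depend on these outcomes.

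The Sample size section treats drop-out as a whole-trial quantity. It says that recruiting 120 patients "will enable us to estimate the recruitment and drop-out rates with a 95% CI of within ±10" per cent, and for half of the patients completing it gives an interval based on 120: "50% of patients completing the study, is 41% to 59" per cent. Only adherence is limited to one arm, with the reason given: "The 95% CI for 30 adherent patients out of 60, as this is only relevant for patients in the intervention group, is 37%–63" per cent.

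The Feasibility outcomes section lists loss to follow-up as a primary outcome without limiting it to an arm. The Study procedure overview has every participant in the study until day 60, with calls to all patients at 30 and 60 days.

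**The concern.** Two features of the row look wrong.

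First, the denominator. Adherence to the module has no meaning for controls, so one arm is right there. Completion applies to both arms, and the sample-size text treats it that way. The article gives no reason for the change in Table 1. A definitive randomised comparison needs follow-up in both arms. In an unblinded study, loss may differ between arms, and a one-arm criterion cannot respond to that.

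Second, the lower limit. A stop needs fewer than one patient in ten to complete. If that limit almost never operates, the row is in practice a two-level rule (*Proceed*, or *Proceed with changes*) presented as a three-level one.

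What is at stake is the decision to go on to the definitive trial. No estimate or safety outcome of the feasibility study itself is affected.

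**Working it through.** **Inputs from the article.** 120 patients, 60 per arm. Table 1 cut-offs of 10% and 60% completion. Intervals of 41% to 59% for 60/120 and 37% to 63% for 30/60, from Stata's `cii proportions`.

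**1. The plan's own figures.** The exact (Clopper-Pearson) limits for x of n are the 0.025 quantile of Beta(x, n − x + 1) and the 0.975 quantile of Beta(x + 1, n − x).

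- 60/120: 40.7% to 59.3%, half-width 9.3 points. This agrees with the stated 41% to 59%.
- 30/60: 36.8% to 63.2%, half-width 13.2 points. This agrees with the stated 37% to 63%.

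The plan's intervals are therefore correct. But a completion criterion counted on 60 patients has the second precision (about ±13), not the first (within ±10), which is the one claimed for drop-out.

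**2. Cut-offs as counts of 60.**

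- *Do not proceed*: below 0.10 × 60 = 6, so 5 or fewer completers (at least 55 of 60 lost).
- *Proceed with changes*: 6 to 35 completers.
- *Proceed*: 0.60 × 60 = 36 or more completers.

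At the boundaries, 6/60 has an exact 95% CI of 3.8% to 20.5%, and 36/60 has one of 46.5% to 72.4%.

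**3. How the row behaves.** With X ~ Binomial(60, p), P(stop) = P(X ≤ 5) and P(proceed) = P(X ≥ 36). The values of p are assumptions that span the range; the article gives no expected completion.

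| True completion p | Do not proceed | Proceed with changes | Proceed |
|---|---|---|---|
| 10% | 44% | 56% | 0% |
| 15% | 9.7% | 90% | 0% |
| 20% | 1.2% | 99% | 0% |
| 30% | 0.005% | >99.9% | 0% |
| 40% | 0% | 99.9% | 0.1% |
| 50% | 0% | 92% | 7.8% |
| 60% | 0% | 44% | 56% |
| 70% | 0% | 3.6% | 96% |

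(0% means below 0.001%.)

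**4. The control arm.** Hold intervention completion at 36/60, which reads *Proceed* on this row, and vary the controls:

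- Controls 18/60: overall (36 + 18)/120 = 45%. The row still reads *Proceed*.
- Controls 0/60: overall 36/120 = 30%. The row still reads *Proceed*.

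These are illustrations of what the rule permits, not forecasts.

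**5. What a wider denominator would cost.** At true completion of 60% in both arms:

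- Present rule: P(X ≥ 36 of 60) = 56%.
- Pooled, 60% of 120: P(X ≥ 72 of 120) = 54%.
- Each arm must reach 60%, arms independent: 0.556 × 0.556 = 31%.

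Pooling alone does not remove the blind spot: 60/60 intervention and 12/60 control completers also give 72/120 = 60%. A rule for arms in different bands is therefore needed as well.

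**The case against.** A reader might infer that the row cannot detect serious attrition at all. The documents do not support that. Intervention-arm loss above 40% already forfeits *Proceed*: at true completion of 50% this happens 92% of the time, and at 40% or below at least 99.8% of the time. Nor does the row act alone. The adherence row gives *Do not proceed* when under 40% of intervention patients send an image, so mass loss before any photo would be caught there. The gap that remains is for patients who send one photo and are lost afterwards.

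It can also be said that planning precision and setting a decision rule are different tasks, so the Sample size section and Table 1 could both stand. That is fair as far as reporting goes: loss to follow-up and its reasons are a primary feasibility outcome, feasibility outcomes carry 95% CIs, and control-arm loss would be seen. But the article ties the decision to the table, and there control-arm loss has no threshold.

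Two further points stand. Nothing in the article shows that controls will be lost more often; participants who complete data collection are offered recompense, and readmissions and further surgery are also taken from case notes. And adherence and completion are different quantities, so the 40% stop limit for adherence does not show that 10% is wrong for completion. The article states no tolerable attrition for the definitive trial, and a condensed article may leave the reasons for its cut-offs to the full protocol.

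**Conclusion.** The point holds in a limited form. The denominator in the loss-to-follow-up row does not match the article's own treatment of drop-out as an outcome in all 120 patients. As written, no amount of control-arm or differential loss can alter this criterion. That follows from the wording and needs no assumption about how much loss will occur.

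The stop band is close to inert: it operates 44% of the time at true completion of 10%, 9.7% at 15% and 1.2% at 20%, assuming 60 intervention patients who complete independently with a common probability. It does not follow that heavy intervention-arm loss goes unnoticed, since it lands in *Proceed with changes*. Nor can one say from the article which level of loss would make the definitive trial unworkable.

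The severity is should-fix. The criterion steers the next trial and is cheap to correct, but the data are collected in both arms and the results will be reported in any case.

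**What to change.** In the third row of Table 1, count all randomised patients instead of intervention patients, and define completion as the 60-day contact. Report completion overall and by arm with exact 95% CIs. State a single rule for arms that fall in different bands; for example, the verdict follows the arm with lower completion.

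Before any results are seen, replace the 10% stop limit with a higher one that the team justifies against the attrition the definitive trial can absorb. This review proposes no figure, because the article gives no basis for one.

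The cost is one table row and a sentence of rationale; the calls at 30 and 60 days already cover all patients. The rule becomes somewhat stricter. At 60% true completion in both arms, the chance of *Proceed* on this row falls from 56% to 31% if each arm must reach 60%. With the pooled denominator alone it is 54%, but pooling alone can hide a large difference between arms.

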### Staff study

All nurses and surgeons at both sites who have been involved in using the Isla platform will be invited by the site research team to complete an online survey. The survey is hosted on Dacima and will take 15 min to complete. The focus of the staff survey is the experience of being involved in the study, experience of using the Isla platform, and experience and views on postoperative surgical wound follow-up. Quantitative survey data will be analysed using simple descriptive statistics. Staff will be invited, via the survey, to participate in an interview. Up to 10 staff will be interviewed.

As the interviews will be remote, consent will be conducted remotely. The researcher will cover the information leaflet and consent form with the participant on the recording, but only the researcher will sign the consent form. The recording of the participant giving consent will be audio recorded and transcribed.

The interviews will be semistructured and focus on the acceptability of the Isla platform and satisfaction with postoperative wound follow-up. All interviews will take place via Microsoft Teams and will be digitally recorded with the permission of the participant. Interviews are expected to last around 40 min. Data from the interviews will be independently transcribed and analysed using thematic content analysis.^22^

### Health economic evaluation

An economic investigation is included as the provision of the intervention will involve additional upfront direct costs. The intervention is unlikely to be widely adopted unless it can be shown to be cost-effective. For the intervention to be cost-effective, the initial upfront cost will need to be offset by savings later in the clinical pathway and, or, deliver positive impacts on health outcomes. The economic investigation will comprise two stages: an initial scoping exercise and an economic evaluation on completion of the clinical study. The scoping exercise has been undertaken to inform the design of this study. This involved a search for relevant economic evaluations and existing evidence base, the development of an early model and the drafting of a health economic analysis plan.

The economic evaluation will compare health outcomes and costs in the intervention and control arms using a probabilistic decision model. This will provide an estimate of the probability of cost-effectiveness of the intervention compared with the standard of care and identify key parameters for cost-effectiveness for further investigation in a clinical trial. We will also explore the impact of different models of providing the intervention service.

### Implementation and adoption strategy

A healthcare adoption plan will be developed which will include stakeholder analysis, identification of potential barriers and facilitators to adoption, and the best route to the NHS market. We will map inclusion of the Wound Imaging Software Digital platfOrM solution in current NHS pathways and processes and maximise our early insight into the evaluation and adoption processes. We will collect the appropriate information during the project, with a view to understanding pathway changes and effect of health economics and end-user requirements on potential adoption.

### Ethics and dissemination

Permission to conduct the study was granted by the North of Scotland Research Ethics Committee 1 (24/NS0005) and the MHRA (CI/2024/0004/GB). The trial was prospectively registered on 15 March 2024 (ISRCTN16900119) with data collection starting in July 2024.

Data arising from the study will be owned by the sponsor and shared with collaborators in accordance with the Terms and Conditions of the study Collaboration Agreement. The study reporting will be in accordance with the Consolidated Standards of Reporting Trials guidelines.^23^ Our PPI group will inform the dissemination strategy. Study participants will be notified of publications via the study newsletters and via email if they choose to provide contact details. Study results will also be shared with stakeholders, identified through a stakeholder mapping exercise. Two publications are planned, which will be published in open-access journals. We will also share a study report and findings on the study website (www.wisdomai.uk) and through social media such as X, formerly Twitter accounts. Anonymised data will be available after study completion on request for research purposes. The clinical investigation will be registered on a publicly accessible database and the results of the investigation will be made publicly available.
